### ***Primary outcome measures***

- ◆ Feasibility: recruitment rate ( $\geq 50\%$ ), adherence to assessment tests ( $\geq 80\%$ ), adherence to supplements ( $\geq 80\%$ )
- ◆ Physical performance from validated tests:
  - 6-minute walk test: distance achieved at normal walking pace for 6 minutes, measured on a 30 m-course; gait speed is also measured during the first 4 m, in m/s. This test assesses the submaximal level of functional capacity and is indicative of mobility limitations; a change of 20 m has clinical relevance.
  - 30-second chair-stand: number of times capable to stand up completely and sit down within 30 seconds, without the aid of armrests (measured in number of chair-stands).
  - Timed-Up-and-Go (TUG): time required to rise from a chair, walk 3 m, turn and come back to sit on the chair, (measured in seconds).
- ◆ Muscle strength:
  - handgrip strength measured with hand-held dynamometer, measured seated, 3 measurements per hand, alternatively (measured in kg)
  - Maximal leg strength (isometric knee extension peak torque) from a 60-degree angle using the Biodex System 4 Pro dynamometer on the dominant side (measured in N).

### ***Secondary outcome measures***

- ◆ Appendicular muscle mass index will be measured by dual energy X-ray absorptiometry (DXA) as the sum of arm and leg lean tissues (without bone mineral content) divided by height squared. This index defines sarcopenia. The test will be performed at the Montreal General Hospital or at the MUHC-McDonnell Centre for Innovative Medicine (Glen site).
- ◆ Voluntary physical activity measured by accelerometry. Participants will wear an ActiGraph® GT3X accelerometer (small belt-held device) during 4 days for each measurement. Instructions will be given on how and when to wear the device. The activity counts, energy expenditure, steps count, activity/sedentary bouts will be collected. An activity logbook will be completed during the same days.
- ◆ Food intake will be estimated from 3-day food diary. Instructions will be given on how to record food intake with portion size estimation with measuring cups and spoons, by a registered dietitian (PI or graduate student). Nutrient analysis will be performed using the Food Processor software (ESHA®).

### ***Other measures and questionnaires.***

- ◆ Blood sample (fasting): complete blood count, full biochemistry, renal profile, A1C, glucose, insulin, TSH, albumin, liver enzymes, C-reactive protein, vitamin D 25(OH). (Most are routine tests at the GDH, others will be requested). Aliquots will be centrifuged and separated, and plasma will be kept at minus 80°C for later analysis of phospholipid fatty acid composition by gas chromatography (GC-MS) and amino acid profile by liquid chromatography-tandem mass spectrometry (LC-MS/MS).
- ◆ Anthropometric measurements: height, weight, waist and calf circumference according to standard procedures.
- ◆ Questionnaires: Mini-Nutritional Assessment- Short Form (MNA-SF): 6-item questionnaire for screening of malnutrition; health-related quality of life (EQ-5D). Scores of Mini-Mental State Examination, Montreal Cognitive Assessment (MoCA), and Barthel index done at the GDH will be collected.

### **STATISTICAL ANALYSIS**

This is a pilot study designed to generate data on feasibility, acceptance and compliance to the supplement and study tests; it is not powered for identifying statistical differences in the main outcomes. The sample size required for the full study will be of approximately 160 participants (80 EXP, 80 CTR). This calculation is based on an expected difference of 1 second in reducing the chair-stand time between the 2 groups, acknowledging that the CTR will also gain from the rehab program, and from standard deviation from published studies. This sample size should be enough to detect differences in handgrip and leg strength and in appendicular muscle mass accretion. Pilot data will therefore be crucial to confirm these calculations. We aim to recruit 40 participants to provide confidence intervals to determine the final RCT sample size.

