Increasing protein intake from dietary sources such as meat, fish, dairy and legumes, in frail elderly persons is a challenge for the majority who have decreased appetite, and for many with mastication and digestibility difficulties, and budget limitations. Because large intakes of protein increase satiety and may induce a compensatory decrease in voluntary food intake, it is important to propose supplements of high-quality protein with fewer calories. Whey protein is naturally rich in essential AA, particularly leucine. It is palatable, easy to digest and dissolvable such that it may be provided as a small volume drink, which should not displace usual food intake. Whey protein supplements provided as 2 doses of 20 g per day were tested in mobility-limited elderly with resistance exercise training during 6 months. Significant improvement in muscle mass and strength, and stair-climbing performance were reported due to exercise but only trends for additional benefits of the whey protein supplement were observed. The dose of 20 g per meal occasion may not have been sufficient to reach the anabolic threshold and, supplements were consumed after breakfast and supper. Our last year study, funded by the Helen McCall Hutchison foundation, revealed that a leucine supplement ingested before meals as opposed to within meals generated greater circulating leucine concentrations (both peak and area under the curve). Thus, timing of supplement ingestion should also be considered when designing an intervention to promote muscle protein anabolism.

A recent randomized placebo-controlled trial tested a whey protein supplement of two doses of 20 g enriched with 3 g leucine and 800 IU vitamin D, in sarcopenic, independently living older adults with mobility limitations. Supplements were ingested before breakfast and lunch during 13 weeks. The intervention resulted in more gain in muscle mass and improved chair-stand test, an indicator of muscle strength and power, compared to placebo. No difference in handgrip strength and global score for physical performance were seen. Authors argued that the dose of whey protein may not have been sufficient to improve all aspects of physical performance.

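### The full-trial size of about 160 is planned on chair-stand time in seconds, but the pilot records only stands completed in 30 seconds, so it cannot confirm that calculation

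*Protocol*

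**What the plan says.** Under STATISTICAL ANALYSIS, the protocol gives the full-trial size as approximately 160, with 80 per arm. The basis is: "This calculation is based on an expected difference of 1 second in reducing the chair-stand time between the 2 groups". The variability is taken "from standard deviation from published studies", with two trials cited and no value given. Alpha, sidedness, power and any dropout allowance are not stated. The section then calls the pilot data crucial for confirming the calculation. It links the target of 40 participants to confidence intervals from which the final trial size will be set.

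Under Primary outcome measures, the chair-stand test is the "number of times capable to stand up completely and sit down within 30 seconds", with the number of stands as its unit. The Timed-Up-and-Go is recorded in seconds, but it is a different task: one rise, a 3 m walk, a turn and a return. Neither Secondary outcome measures nor Other measures and questionnaires lists a timed chair-stand.

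STATISTICAL ANALYSIS adds: "This sample size should be enough to detect differences in handgrip and leg strength and in appendicular muscle mass accretion". It gives no difference or SD for any of these three outcomes.

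**The concern.** The planning quantity and the measured quantity are different variables. In a timed chair-stand the number of stands is fixed and the time varies. In the 30-second test the time is fixed and the number varies. Improvement is a fall on the first scale and a rise on the second. The pilot will yield an SD and a confidence interval in stands, and neither can be set against a difference of 1 second or an SD in seconds.

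An analysis plan could not repair this afterwards, because the timed variable is not listed for collection and cannot be recovered from a count. What is at stake is one of the pilot's stated uses. The SD determines the size of the later trial, and on the scale used for 160 the pilot will provide no SD.

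The sentence on handgrip, leg strength and muscle mass extends 160 to three further outcomes without giving any basis that a reader could check.

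**Working it through.** **1. Can 160 be reproduced?** The inputs given under STATISTICAL ANALYSIS are n = 80 per arm and a difference of 1 s. SD, alpha, sidedness, power and dropout are missing, so the figure cannot be reproduced directly. It can be solved backwards for the SD it implies, using the normal approximation for two means:

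SD = difference × √(n/2) / (z_alpha + z_power), with √(80/2) = 6.325.

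| Assumed alpha 0.05 | z_alpha + z_power | Implied SD |
|---|---|---|
| two-sided, 80% power | 1.960 + 0.842 = 2.802 | 6.325 / 2.802 = 2.26 s |
| two-sided, 90% power | 1.960 + 1.282 = 3.242 | 6.325 / 3.242 = 1.95 s |
| one-sided, 80% power | 1.645 + 0.842 = 2.487 | 6.325 / 2.487 = 2.54 s |
| one-sided, 90% power | 1.645 + 1.282 = 2.927 | 6.325 / 2.927 = 2.16 s |

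An exact t-test calculation changes the two-sided values only slightly, to 2.24 and 1.94 s. If 160 already includes 10 to 20% dropout (72 to 64 evaluable per arm), the two-sided values run from 2.14 s (80% power, 10%) down to 1.75 s (90% power, 20%). So an SD of about 1.7 to 2.5 s yields 160 under ordinary choices.

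**2. How much depends on that SD?** With a 1 s difference, two-sided 5% and 80% power, n per arm = 2 × 2.802² × SD² = 15.70 × SD², rounded up:

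- SD 2.0 s: 63 per arm
- SD 2.5 s: 99 per arm
- SD 3.0 s: 142 per arm

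The SD in seconds is therefore the quantity that most needs confirming.

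**3. Can the count stand in for the time?** The protocol does not say how many stands the chair-stand time covers. Assume five stands at constant pace. The count in 30 s is then 30 × 5 / T = 150/T, where T is the five-stand time. The gain in count from a 1-second improvement is 150/(T − 1) − 150/T:

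| From T to T − 1 | Count before → after | Gain in stands |
|---|---|---|
| 30 → 29 s | 5.00 → 5.17 | 0.17 |
| 25 → 24 s | 6.00 → 6.25 | 0.25 |
| 15 → 14 s | 10.00 → 10.71 | 0.71 |
| 10 → 9 s | 15.00 → 16.67 | 1.67 |

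The baselines are illustrative. The relation is reciprocal, so the worth of 1 second depends on where the participant starts. Neither a mean difference nor an SD can be carried across by a single factor. A corrected size in stands cannot be computed, because the protocol gives neither a target difference nor an SD in stands.

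**4. What does 80 per arm detect on any continuous outcome?** At two-sided 5% and 80% power with no dropout, the standardised difference is 2.802 / 6.325 = 0.443 by the normal approximation and 0.446 by the t-test, or about 0.45 SD. Whether that is enough for handgrip, leg strength or muscle mass depends on differences and SDs that the protocol does not state.

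**The case against.** The case for leaving the text alone has several parts.

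*The 160 is not this trial's size.* Allocation, outcomes, feasibility thresholds and the 40 participants do not derive from it. This stands, and it limits the severity.

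*Confirming the calculation is not the pilot's only purpose.* Under OBJECTIVES, feasibility, acceptance, compliance and safety come first, and STATISTICAL ANALYSIS opens on feasibility. A reader might infer that the mismatch defeats the pilot as a whole. It does not. It defeats one stated use.

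*The 160 is already provisional.* It is described as approximate, and the final size is to be set after the pilot. A reader might infer that 160 will be carried forward unchecked, but the text does not say so. The pilot will give SDs for stands, handgrip, leg strength, walking distance and muscle mass, any of which could support a new calculation. Only confirmation of the calculation as written is lost.

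*The handgrip result in the cited trial.* BACKGROUND reports, for an earlier trial of whey protein with leucine and vitamin D, "No difference in handgrip strength and global score for physical performance were seen". A reader might take this as evidence that 160 is too small for handgrip. That trial differed in whey and vitamin D dose, timing, duration and population, and no omega-3 is described. It also reported a greater gain in muscle mass. The fault in the sentence about these outcomes is its missing basis.

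*Forty participants give imprecise estimates.* They do, but that is true of any pilot of this size, and the protocol says that it is not powered for group differences. It is a separate matter from the unit mismatch.

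None of these points removes the mismatch between the planned and the measured variable.

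**Conclusion.** The inconsistency is real and lies wholly within the protocol. The full-trial size rests on a difference in chair-stand time, the pilot collects a count, and the pilot is nevertheless said to confirm the calculation. This conclusion needs no assumption about the SD, alpha or power. The figures in stands assume five stands at constant pace and only illustrate that no fixed conversion exists.

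A reader might go further and conclude that 160 is wrong. The documents do not support that: an SD of about 1.7 to 2.5 s reproduces it under usual error rates, and the published SDs are not in the protocol. The statement about strength and muscle mass is unsupported, but it is not shown to be false.

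This should be fixed. It concerns the planning of the later trial and leaves the validity of the pilot's own results untouched.

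**What to change.** **Preferred.** Rewrite the paragraph so that the full-trial calculation uses the measured outcome: a target difference in 30-second stands with its justification, the SD of that count to be taken from the pilot, alpha with sidedness, and power. State that 160 came from a different chair-stand measure and will be replaced by this calculation.

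**Alternative.** Keep the seconds-based calculation, and also record the time to a fixed number of stands during the same 30-second test. The number must match the measure used in the cited trials. A rule is needed for participants who do not reach it, since a frail participant may complete too few stands to have a time. This has to be in place while data are being collected.

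**In either case.** State the SD, alpha and power behind 160 for as long as the figure is quoted. Delete the sentence on handgrip, leg strength and muscle mass, or replace it with what 80 per arm detects: about 0.45 SD at 80% power, two-sided 5%, before dropout.

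**Cost.** One reworded paragraph and, for the alternative, one extra field on the test form. The planned size of the full trial may change in either direction.

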### **ETHICAL CONSIDERATIONS**

All participants will provide written informed consent. Participants of both arms will benefit from a full nutritional counseling by the PI or the graduate student involved in this study, to optimize their nutritional intake in addition to the standard of care of the GDH program. Those randomized to the EXP group might further benefit from the supplement, in improving muscle mass strength and physical function, according to our hypothesis.

***Intervention products and doses:*** The whey protein isolate, leucine and maltodextrin (placebo) powders are commercially available for human use and safe to ingest at the proposed doses. All will be purchased from ProteinCo Canada, Cowansville, QC, which certifies a Pharmaceutical Grade Purity. These powders are fairly easy to dissolve in water with some mixing and have a sweet taste. The total amount of protein supplemented per day (36 g, 45 g or 54 g) will increase total daily protein intake to 1.2-1.5 g/kg/day, depending on current intake. This range is recommended by at least two international expert groups and recognized as safe for the older population. This dose is however not recommended for persons with severe kidney diseases; therefore, those having such diagnosis or an estimated glomerular filtration rate (eGFR) below 30 mL/min/SA will not be eligible to participate. The free leucine (3 g) added to the whey protein will total 6 g, twice per day = 12 g, which is below the tolerable upper intake level (UL) and safe limit in humans of >550 mg/kg/d, equivalent to 30-39 g/d depending on

weight. The leucine purity, of 99%, has been confirmed by LC-MS/MS and will be assessed for new lots purchased.

Vitamin D: the daily doses of  $\geq 1966.7$  IU (1966.7 IU, 1983.3 IU or 2100 IU depending on the body weight) of vitamin D3 is desirable to augment and reach serum 25(OH)D of  $\geq 80$  nmol/L, based on several studies mostly on osteoporosis and fractures; it is well below the tolerable upper intake level of 4000 IU/day (DRIs) for adults >70 years.

Omega-3 fatty acids: Typical side effects include fishy aftertaste and burping, but these possible effects will be minimized by the choice of fish oil supplement NutraSea (from Ascenta) that is fruit-flavored (grapefruit/tangerine or apple). There is no UL determined for *n*-3 FAs. However, the European Food Safety Authority has established that supplemental doses up to 5 g/day “do not raise safety concerns for adults”. Our proposed daily dose of 2 g is less and has been used in several other studies in older adults, of longer duration.

*Potential risks:* as with any change in diet, dietary supplements may be associated with gastrointestinal adaptations at the onset (e.g. constipation or softer and more frequent stools), which typically resolve with time. If persisting, these will be addressed by dietary recommendations from the PI or graduate student (both RDs) or prescription of laxatives (by the study MD). The functional tests proposed are standard and specific to the geriatric population, will be performed by trained physiotherapists of the GDH and should cause no harm. Any serious and non-serious adverse event will be recorded.

*Financial compensation:* participants will not receive an honorarium for this study. Their transport or parking fees for the three assessment visits (baseline, 8 weeks and 16 weeks) at the Royal Victoria Hospital (Glen site) will be reimbursed.

## **SIGNIFICANCE**

The combined whey protein, leucine, vitamin D and omega-3 FAs supplement was carefully designed with appropriate dosages and timing of ingestion to be both relevant to study outcomes and practical to ensure compliance. This pilot study is a natural extension of our previous studies. It will help define the feasibility of implementing the proposed nutritional intervention in the GDH program to eventually extend to a larger RCT rigorously assessing the potential benefits of the supplement in improving physical performance of GDH participants and gaining back some losses of autonomy.

## Appendix

**Table 1. Information on Dietary Supplements to be used**

| Supplement and ingredients                                                                                | Brand Name/Company                                             | Health Canada NPN | Daily Dose ingested                                                                                                   | UL                                    |
|-----------------------------------------------------------------------------------------------------------|----------------------------------------------------------------|-------------------|-----------------------------------------------------------------------------------------------------------------------|---------------------------------------|
| Experimental supplement                                                                     |                                                                |                   |                                                                                                                       |                                       |
| Whey protein isolate (vanilla flavored)

- Protein (27g/30g dose)
- Vitamin D3 (100 IU/30g dose) | New Zealand Whey Protein Isolate/ The Protein Company ATW Inc. | 80054732          | 2 x 20 g = 40 g
2 x 25 g = 50 g
2 x 30 g = 60 g

36 g
45 g
54 g

66.7 IU
83.3 IU
200 IU | N/A

4000 IU/d                  |
| Leucine                                                                                                   | ProteinCo Leucine Powder/ The Protein Company ATW Inc.         | 80062837          | 2 x 3 g = 6 g                                                                                                         | 550 mg/kg/d                           |
| Fish oil containing vitamin D (flavored) :
- EPA
- DHA
- Vitamin D3                              | NutraSea +D/ Ascenta                                           | 80050462          | 7.5 mL oil =

1125 mg
750 mg
1500 IU                                                                      | EPA + DHA :
5 g/d

4000 IU/d |
| Placebo supplement                                                                          |                                                                |                   |                                                                                                                       |                                       |
| Maltodextrin                                                                                              | Maltodextrin Powder/ The Protein Company ATW Inc.              | 80054728          | 2 x 30 g = 60 g                                                                                                       | N/A                                   |
| Corn Oil                                                                                                  |                                                                | N/A               | 7.5 mL                                                                                                                | N/A                                   |

UL: Upper Tolerable Level; EPA : eicosapentaenoic acid; DHA : docosahexaenoic acid; N/A: not applicable
